### Sample size

We conducted a power analysis using Monte Carlo data simulation. We conducted the analysis using a mixed effects model with a fixed effect of chemotherapy cycle (time) and random effects for slope and intercept by participants with unstructured correlation [33–36]. Cheng [35] et al. suggest the use of unstructured correlation when time is used as a fixed effect (chemotherapy cycle) and we are not making specific assumptions about the shape of the curve. Due to limited studies of NIRS measurements of patients with cancer, we used the conservative estimate of average recovery kinetics time constant (τ) of patients with chronic heart failure (25.35 seconds) and extrapolate average change in τ throughout chemotherapy from Foulkes using results from Beever [37,38]. We assume that the random intercept will follow a gamma distribution with shape 1.57, a scale of 12.5, and a right shift of 13.25. Additional assumptions from Foulkes [38] and Beever [37] include the random slope is assumed to follow a normal distribution with an extrapolated standard deviation, as well as a normal distribution of the error with standard deviation of 5.54 [39,40]. Analysis indicates that using a linear mixed effects model with sample size of at least n = 30 will be able to detect an effect of chemotherapy on τ with a power of 0.8. Due to potential dropout or missing data, data collection will continue until data is collected on 30 subjects who have completed the study. As the effect of chemotherapy type on τ is unknown and unable to be approximated with data simulation, we are unable to conduct a full power analysis with the effect of chemotherapy type on τ [29,41,42]. Based on treatment regimens of pilot data, chemotherapy type can be divided into cytotoxic (platinum-based, anthracyclines, etc.) for 3–4 cycles and non-cytotoxic such as immunotherapy for an additional 3–4 cycles. In some cases, treatment would be given concurrently and could be treated as a separate group of cytotoxic + non-cytotoxic. We assume that at least n = 8 of each chemotherapy type will be necessary to detect any differences in trajectory of τ over time consisting of 3 or more cycles of chemotherapy Comparisons between drug regimens could be adjusted based on updates to the NCCN guidelines.

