Assessment of mitochondrial capacity with NIRS includes studies of clinical populations with peripheral artery [27], chronic kidney [24], and neurologic diseases such as traumatic spinal cord injury and multiple [22], as well as comparisons with healthy [28] and age-related differences in skeletal muscle oxidative [17]. However, there is a dearth of NIRS studies examining the effects of chemotherapy on skeletal muscle mitochondrial function in patients with cancer. Only two studies to our knowledge have utilized NIRS to measure muscle oxygenation variables in cancer survivors. Ederer, et al. [29] determined that [HHb] and [Hb]total were significantly lower in eight cancer survivors (all eight received chemotherapy and five received radiation) compared to healthy controls during exercise at ventilatory threshold. Grigoriadis et al. [30], did not find a significant difference in muscle oxygenation variables between 23 patients with breast cancer (16 received chemotherapy, nineteen received radiation therapy, and 21 received hormonal therapy) and 23 participants who served as age and BMI matched controls. Recent literature of near infrared spectroscopy related to cancer primarily involves detection and identification of cancerous [31] or the use of near infrared light as a photoimmunotherapy [32]. Therefore, the hypothesized loss of mitochondrial capacity throughout chemotherapy treatment has not been studied longitudinally starting at baseline and tracking through the chemotherapy regimen in breast and gynecologic cancer patients with NIRS to date.

The aims of our study are to develop a protocol that 1) assesses mitochondrial dysfunction in cancer patients using exercise that is tolerable for the patients throughout the entire chemotherapy regimen and 2) observe the changes in mitochondrial functional capacity between different chemotherapy regimens for each chemotherapy cycle. The protocol also will help us evaluate a potential correlation between subjective self-reported fatigue and perceived effort with corresponding objective whole-body metabolic measurements and NIRS measurements. The proposed study will help inform clinical decision makers in the oncology community regarding current chemotherapy regimens (based upon the National Comprehensive Cancer Network, NCCN) that patients may best tolerate for cachexia and fatigue.

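### The 8 patients per chemotherapy type are not derived, and the planned per-cycle ANOVA would at that size detect a difference in τ of only about 25 s, not any difference in trajectory

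*Protocol article*

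**What the plan says.** The Sample size section of the protocol article justifies 30 completers for the overall effect of chemotherapy by simulation, a size that "will be able to detect an effect of chemotherapy on τ with a power of 0.8". The simulation inputs include a random intercept following a "gamma distribution with shape 1.57, a scale of 12.5, and a right shift of 13.25" and "a normal distribution of the error with standard deviation of 5.54". For the third variance component it says only that "the random slope is assumed to follow a normal distribution with an extrapolated standard deviation".

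For chemotherapy type, the section says "we are unable to conduct a full power analysis with the effect of chemotherapy type on τ", because that effect is unknown. It then continues: "We assume that at least n = 8 of each chemotherapy type will be necessary to detect any differences in trajectory of τ", over three or more cycles. Two types are described (cytotoxic and non-cytotoxic), with concurrent treatment as a possible third.

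The Experimental design section and the Data analysis and statistical analysis section both give the Aim 2 analysis as ANOVAs between regimens at each chemotherapy cycle. The Introduction says the study will "help inform clinical decision makers in the oncology community regarding current chemotherapy regimens", with reference to how well patients tolerate them.

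**The concern.** An unknown effect prevents a conventional power calculation. It does not prevent stating what difference a given group size could detect, which needs only the group size and the variances. The article instead gives a group size and ties it to detecting any difference, with nothing to support the 8.

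The sentence and the analysis also address different quantities. A difference in trajectory is a difference in within-patient change. An ANOVA at one cycle compares levels between different patients, so the large between-patient spread in τ counts in full.

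At stake is what Aim 2 can conclude. If the comparison can see only very large differences, a non-significant result says little about whether regimens differ. A significant result from small non-randomised groups is likely to overstate the difference. Neither is a good basis for a statement about regimens.

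**Working it through.** **The stated figure.** The 8 per type cannot be reproduced, because no effect size, significance level or power is attached to it. The check therefore solves for the difference that 8 versus 8 could detect.

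**Inputs from the Sample size section.** Gamma shape 1.57, scale 12.5, shift 13.25; error SD 5.54 s; stated mean τ 25.35 s. **Assumed here:** two-sided 5%, 80% power (stated for the overall effect only), independent groups, and slopes uncorrelated with intercepts. The slope SD is not given and is varied.

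**Variances**
- Intercept SD = 12.5 × √1.57 = 15.66 s.
- Single-visit SD = √(15.66² + 5.54²) = 16.61 s.
- Mean of the stated gamma = 1.57 × 12.5 + 13.25 = 32.875 s, which is not 25.35 s.

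**(a) Levels at one cycle (the stated ANOVA)**
- Two groups of 8, non-central t: standardised difference 1.507. Detectable difference = 1.507 × 16.61 = 25.0 s (23.3 s by the normal approximation).
- Ratio to the mean of the same distribution: 25.0 / 32.875 = 76%.
- Power is 9% for a true 5 s difference and 20% for 10 s. Simulation from the skewed gamma plus normal error agrees at 5 s (9%) and gives 82% at 25.35 s.
- Three groups of 8: f = 0.68, or 24.0 to 27.7 s between the extreme groups, depending on the pattern of means.
- Slope variance adds to this. Two cycles after baseline, a slope SD of 2 s per cycle gives √(276.0 + 4²) = 17.09 s and 25.8 s detectable. A slope SD of 5 gives √(276.0 + 10²) = 19.39 s and 29.2 s.
- If the scale were 7.7, the mean would be 1.57 × 7.7 + 13.25 = 25.34 s, close to the stated 25.35 s. The SD would be √((7.7 × √1.57)² + 5.54²) = 11.13 s, and the detectable difference 16.8 s, or 66% of the mean.

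**(b) Change over three visits (two cycle intervals)**

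The intercept cancels. SD of change = √((2 × slope SD)² + 2 × 5.54²), multiplied by 1.507.

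| Slope SD (s per cycle, assumed) | SD of change (s) | Detectable difference (s) |
|---|---|---|
| 0 | 7.83 | 11.8 |
| 2 | 8.80 | 13.3 |
| 5 | 12.70 | 19.1 |

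Adjusting for baseline instead of subtracting it changes little. With slope SD 0 the residual SD is 7.61 s and the detectable difference 11.5 s. At slope SDs of 2 and 5 it is 13.0 s and 18.9 s. With four visits and a fitted slope, the detectable difference over the period is 11.2 s at slope SD 0, 14.4 s at 2 and 25.2 s at 5.

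Even at slope SD 0, power for a true 5 s difference in change is only about 22 to 23%.

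**The case against.** The article is candid. It says that it assumes the 8, that this many are necessary (not that they suffice), and that no full power analysis was possible. The Abstract and Discussion call the study a pilot. This limits the criticism: nothing is miscalculated, and no claim of 80% power is made for Aim 2. It does not supply a basis for 8, even as a minimum, and it does not support the phrase about detecting any differences.

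A reader might go further and infer that 8 per type could detect only differences about as large as the whole mean τ, since 25.0 / 25.35 = 99%. The documents do not support that, for two reasons. The sentence concerns trajectories, where the 15.66 s between-patient SD drops out; the result then depends on a slope SD that is not given. The ratio also takes its SD from the stated gamma and its mean from a different figure. Consistent pairs give 76% or 66%.

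The opposite shortcut fails too. A flat statement that a baseline-adjusted analysis detects about 11 s holds only at slope SD 0, and so is a best case.

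The check also assumes that different patients form the groups. The Sample size section describes cytotoxic cycles followed by additional non-cytotoxic cycles, so the same patients may contribute to both types. In that case the 8-versus-8 model does not apply directly, and the worry that 30 completers might not yield 8 per type is weaker.

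Finally, the article defines no clinically important difference in τ and nowhere says that a null result would be read as equal tolerability. The risk of misreading is the reviewer's inference. It rests on the Introduction's aim of informing decisions about regimens, which is itself worded only as helping to inform.

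**Conclusion.** The point holds in limited form. The 8 per type is an underived assumption, and the claim that it serves to detect any differences in trajectory is unsupported. The stated analysis does not test trajectories.

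For the per-cycle ANOVA, the stated variances give a detectable difference of about 25 s, and more with slope variance. It would be 16.8 s if the gamma scale were the value that restores the stated mean. For change over three visits it is at least about 11 to 12 s, rising to about 13 s and 19 s at assumed slope SDs of 2 and 5 s per cycle.

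All figures assume two-sided 5%, 80% power and independent groups. The effect of slope variance also assumes slopes uncorrelated with intercepts. The article specifies an unstructured correlation without giving a value, and a negative one could reduce the spread of levels.

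**What to change.** Replace the sentence on 8 per type with wording such as: *Aim 2 is exploratory. Eight patients per type is not a powered size. With 8 independent patients per type, an ANOVA at a single cycle has 80% power (two-sided 5%) for a difference in τ of about 25 s or more; a comparison of change or trajectory has it for at least about 11 to 12 s, the exact value to be computed with the slope SD used in the simulation.* Before these figures are printed, the sponsor should state that slope SD and reconcile the gamma parameters (mean 32.875 s) with the stated mean of 25.35 s.

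Make the analysis match the question by adding a regimen-by-cycle term to the mixed model, or by comparing regimens with adjustment for baseline τ. Say whether one patient can contribute to more than one type. Report estimates with 95% confidence intervals.

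Soften the Introduction's sentence so that the regimen results are described as preliminary and not as a basis for choosing between regimens.

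The cost is wording, a revised Aim 2 model on data already being collected, and one short calculation from inputs the sponsor holds. No extra enrolment is needed. The stated capability of Aim 2 becomes more modest.

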### Experimental design

We will use an observational mixed model repeated measures design to longitudinally compare (pre-chemotherapy and throughout treatment) patients’ skeletal muscle mitochondrial capacity of the vastus lateralis during stationary cycling. ANOVAs will be used to assess this same mitochondrial capacity between chemotherapy regimens at each chemotherapy cycle. Pearson or spearman correlations will be used to assess relationships between self-reported fatigue and effort values and metabolic measurements (whole-body as well as NIRS). The study population will include female patients with breast or gynecological cancer. All testing will take place in the University of South Carolina School of Medicine Greenville’s Human Performance Laboratory in the Prisma Health Cancer Institute.

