#### Data analysis and statistical analysis.

The following values from the NIRS device will be used to assess both aims: 1) mitochondrial capacity change over time (chemotherapy cycle) and 2) between drug regimens. Previous literature has shown that oxygenation levels at rest after moderate and/or high intensity exercise or after occlusion follows an asymptotic curve of the form [54]:

$$\begin{array}{c} y=A+\left(B_{0}-A\right)e^{-\tau /t} \end{array}$$
(1)

Where *y* is the oxygenation at time *t*, *A* is the oxygenation as *t* approaches infinity*, t* is time measured in seconds, B_*0*_ is the value at *t = 0*, and *τ* is the time constant. For each rest period, we will run an asymptotic regression for O2Hb, HHb, and TSI by time in seconds to find the coefficient estimate for *τ*.

Each data set will contain three rest periods; therefore, each data set will have three *τ* values for each variable. We will average the τ values to obtain one average rest τ for O_2_Hb, HHb, and TSI per data set. Since continuous wave NIRS devices measure oxy- and deoxyhemoglobin as changes from baseline, raw oxy- and deoxyhemoglobin values will have no meaning and are not comparable except when measured as changes over time or as τ values.

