We will analyze the *ΔO*_*2*_*Hb,* Δ*HHb,* and *ΔTSI*, calculated as the change in steady state levels of O_2_Hb, HHb, and TSI respectively from work to rest, with steady state values calculated as the mean value of the final thirty seconds of the stage. For each data set of one on-off kinetics, there will be three work/rest period pairs therefore we will calculate three delta values and average the three delta values to obtain one delta value for O_2_Hb, HHb, and TSI per data set. The three work/rest transitions will allow for reliability testing with intraclass correlation coefficients. For participant data to be included in the final analysis, the participant will need to complete at least three on-off kinetic laboratory visits. Each participant will complete an on-off kinetics at least two weeks apart, but not more than one month apart in accordance with their prescribed chemotherapy treatment regimen. Each on-off kinetics will correspond with the first infusion of a chemotherapy cycle. To allow participants a maximum amount of time to recover from infusions before participating in exercise, the corresponding on-off kinetics takes place within 48 hours of the first infusion of the subsequent chemotherapy cycle. Since chemotherapy treatments vary depending on oncologist recommendation, each participant may complete different lengths of treatment, resulting in each participant having different numbers of data points. This will prevent us from using traditional statistical analysis such as repeated measures ANOVA. Since it is not time itself, but rather the compilation of chemotherapy infusions over time that we predict will cause changes in measures of mitochondrial oxidative function, we will treat the number of chemotherapy cycles as an ordinal variable in this analysis. We will complete an analysis using mixed effects models to predict τ and deltas from the number of chemotherapy treatments with a random intercept for patients. For aim 2, ANOVAs will be used to assess differences in mitochondrial capacity between drug regimens at each chemotherapy cycle.

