### Trial status

The trial is currently in the data collection phase with 26 participants who have completed the protocol. The study is planned to continue to enroll test subjects until n = 30.

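### Aim 2 leaves its regimen groups open with 26 of 30 patients completed, and tests regimens by a separate ANOVA at each cycle on several NIRS outcomes with no deciding comparison

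*Protocol article*

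**What the plan says.** **Groups.** The Sample size section splits chemotherapy type into cytotoxic and non-cytotoxic and adds: "In some cases, treatment would be given concurrently and could be treated as a separate group of cytotoxic + non-cytotoxic". It ends: "Comparisons between drug regimens could be adjusted based on updates to the NCCN guidelines". No cut-off date is attached to either sentence. The same section says that a full power analysis for chemotherapy type was not possible. It assumes at least 8 patients per type, to detect differences in how τ develops over three or more cycles.

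**Test.** Experimental design: "ANOVAs will be used to assess this same mitochondrial capacity between chemotherapy regimens at each chemotherapy cycle". Data analysis and statistical analysis: "ANOVAs will be used to assess differences in mitochondrial capacity between drug regimens at each chemotherapy cycle".

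**Outcomes.** The analysis section opens with "The following values from the NIRS device will be used to assess both aims". It then defines three time constants ("We will average the τ values to obtain one average rest τ for O_2_Hb, HHb, and TSI per data set") and three work-to-rest changes for the same signals, six values in all. The section on first and subsequent visits can be read more narrowly, as τ and TSI. No outcome is named as the deciding one for Aim 2.

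**Status and use.** Trial status: "The trial is currently in the data collection phase with 26 participants who have completed the protocol", against a target of 30. Introduction: "The proposed study will help inform clinical decision makers in the oncology community regarding current chemotherapy regimens". The Abstract and the Discussion call the study a pilot that will supply feasibility and preliminary data.

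**The concern.** Three stated choices combine.

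- The groups to be compared are provisional although 26/30 = 87% of the planned participants have finished. A regrouping now could be made by people who can see the outcomes.
- The method yields one F test per cycle per outcome, and none is marked as the result on which a regimen statement would rest.
- The test does not match its sample-size rationale. An ANOVA at one cycle compares mean levels, whereas the 8 per type is argued from differences in trajectory.

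At stake is whether a reader could tell a chance difference at one cycle from a real regimen effect, in a study that says it will help inform clinicians about regimens.

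**Working it through.** **The plan's own figure.** The only stated power is n = 30 for 0.8, and it belongs to Aim 1. It cannot be reproduced, because the mean slope, the slope SD, alpha and the number of cycles are not given. Aim 2 has no stated power or error rate.

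**Inputs from the Sample size section.**
- Random intercept: gamma, shape 1.57, scale 12.5. SD = √1.57 × 12.5 = 15.66 s.
- Error SD: 5.54 s.
- Correlation between cycles within a patient, ignoring the slope: 15.66² / (15.66² + 5.54²) = 245.3 / 276.0 = 0.89.
- Total SD of τ at one cycle: √276.0 = 16.6 s.
- Eight patients per type, three types if concurrent treatment is separate.
- Cycles: 3–4 plus a further 3–4, so 3 to 8 were examined.

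**Assumptions.** 5% per ANOVA without adjustment; correlation between outcomes 0.5 to 0.8; the variance structure of τ applied to the other outcomes; every group present at every cycle.

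**Upper bound if tests were independent**, 1 − 0.95^m:
- One τ: 14% (m = 3) to 34% (m = 8).
- Six outcomes: 60% (m = 18) to 91% (m = 48).

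These overstate the risk because cycles within a patient are strongly correlated.

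**Simulation allowing for correlation, no regimen effect.** Chance of at least one p < 0.05 over 3 to 8 cycles:

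| Outcomes tested | One grouping, 3 × 8 patients | One grouping, 3 × 10 patients, gamma intercept, random slope | Free choice of grouping |
|---|---|---|---|
| One τ | 8–15% | 7–13% | 15–24% |
| Two (τ and TSI) | 16–25% | 15–24% | 30–42% |
| Six, correlation 0.5–0.8 | 26–46% | 24–50% | 43–69% (3 × 8), 43–75% (3 × 10) |

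The two-outcome figure with free grouping comes from the 3 × 10 version. Free choice means three groups, or the concurrent group merged into either of the others, with any significant result counted. If the six outcomes were uncorrelated, the 3 × 10 version with one grouping gives 41–58%.

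**What one per-cycle comparison can detect.** With 8 per group, 80% power and two-sided 5%, the standardized difference between two groups is about 1.51. In seconds: 1.51 × 16.6 ≈ 25 s. The article's assumed average τ is 25.35 s, so a single cycle can reliably show only a difference about as large as τ itself.

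**What a slope comparison can detect.** The formula is 1.507 × √(slope SD² + 5.54² / Sxx), where Sxx is the sum of squares of the visit times about their mean. For baseline plus three cycles (times 0, 1, 2, 3), Sxx = 5.
- Slope SD 0: 1.507 × √(30.69 / 5) = 3.7 s per cycle, or 11 s by the third cycle.
- Slope SD 2 (assumed): 1.507 × √(4 + 6.14) = 4.8 s per cycle, or 14 s by the third cycle.

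Both are well below 25 s, because stable differences between patients drop out of the slope.

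**The case against.** Much can be said for the plan.

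- The article condenses a fuller plan that is not shown. Alpha, hierarchy and adjustment may be set there. A reader might infer that every ANOVA is run at full 5%, but the article does not say so. This stands: 5% is an assumption here.
- A reader might infer that a false regimen finding is more likely than not. With one grouping and correlated outcomes it is not. TSI is computed from O2Hb and HHb, so high correlation between outcomes is plausible. The limit of 300 minutes in total, at up to 60 per session, allows five full-length sessions: the lactate test, a baseline and three follow-ups. That points to the low end of the cycle range. This also stands.
- A reader might infer that groups would be chosen to suit the results. The stated trigger is an external guideline, and nothing indicates that outcomes have been examined by regimen. Merging the concurrent group into another is a possibility left open, not a stated plan. This stands against any charge of selection. It does not supply the missing cut-off, and the choice about concurrent treatment has no external trigger.
- The study is called a pilot, Aim 2 is framed as observing, and the lack of power is conceded. This weakens any claim that results would be issued as clinical guidance, but it leaves the Introduction's sentence about clinicians at odds with the pilot label.

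The objections do not reach the per-cycle method. It is stated in two sections, and it does not test the trajectory used to justify n = 8.

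**Conclusion.** The point holds in a limited form. Aim 2 has provisional groups with 87% of participants completed, a stated per-cycle test on several outcomes with none deciding, and a mismatch between that test and the rationale for 8 per type. Under the assumptions above, the chance of at least one spurious regimen difference exceeds 5% in every scenario. The level depends mainly on how many outcomes are tested, and the working table gives the ranges. At outcome correlations of 0.5 to 0.8, it passes 50% only when six outcomes and open grouping are combined. The article does not support calling a false finding likely, saying that unadjusted 5% tests are planned, or saying that groups will be picked from the data. The issue should be corrected, and the correction is still most credible before outcomes are tabulated by regimen.

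**What to change.** 1. Define the regimen groups now from the agents received. State how concurrent treatment is classed, and how patients who pass from cytotoxic to non-cytotoxic cycles are handled. Do this before any NIRS outcome is tabulated by regimen. Replace the last sentence of the Sample size section with a statement that later NCCN changes do not regroup enrolled patients.
2. Make the main Aim 2 comparison one joint regimen-by-cycle test in the mixed model, on one named τ. With the groups fixed, its nominal error rate is 5%. Keep in that model the random slope described under Sample size, since the analysis section lists only a random intercept.
3. Report the per-cycle ANOVAs and the other outcomes as exploratory estimates with intervals, without significance claims.
4. Reword the Introduction's sentence about clinical decision makers so that Aim 2 generates hypotheses about regimens, in line with the pilot label.

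The cost is wording only, with no further patients or data. The small downside is that p-values at single cycles can no longer be presented as regimen findings.
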